### Definition of analysis sets

(1) Full analysis set (FAS): All participants randomly assigned to the group, use the medicine at least once, and have at least one visit will be analyzed using intention-to-treat analysis of the entire dataset.(2) Per protocol set (PPS): This includes all participants who comply with the research protocol, which have no missing data on important baseline variables and primary outcome. Major violations on concomitant medicine and extremely lower compliance will be considered to be excluded from PPS.(3) Safety set (SS): All randomized participants could be included in SS if they have used at least one dose of drugs and have completed at least a one-time safety assessment. Impution will not be conducted for safety outcomes in SS.

### Descriptive statistics

Participants' baseline characteristics will be reported in a baseline table for each randomization group, and baseline data and descriptive statistics will be assessed using standard measures in accordance with the recommendations of the consolidated standards of reporting trials (CONSORT) guidelines (Moher et al., 2010). (Table 2). The table describes the following variables: age, sex, height, weight, clinical symptoms, and medical and treatment histories. The sample is displayed in accordance with the entire analysis set. Baseline characteristics will be compared between the groups.

**Table 2 T2:** Baseline demographic and clinical characteristics.

Variables	SHHS Group (n=xx)	LHQW Group (n=xx)	All participants (n=xx)	*P-value*
Age (year)^a^	xx (xx)	xx (xx)	xx (xx)	.xx
18≤Age<65	xx (xx)	xx (xx)	xx (xx)	.xx
Age≥65	xx (xx)	xx (xx)	xx (xx)	.xx
Males sex^b^	xx (xx%)	xx (xx%)	xx (xx%)	.xx
Height (cm)^a^	xx (xx)	xx (xx)	xx (xx)	.xx
Weight (kg)^a^	xx (xx)	xx (xx)	xx (xx)	.xx
Vital signs				
Heart rate (beats/minute)^a^	xx (xx)	xx (xx)	xx (xx)	.xx
Respiratory rate (breathe / minute) a	xx (xx)	xx (xx)	xx (xx)	.xx
Pulse Rate (beats/minute)^a^	xx (xx)	xx (xx)	xx (xx)	.xx
Systolic blood pressure (mmHg)^a^	xx (xx)	xx (xx)	xx (xx)	.xx
Diastolic blood pressure (mmHg)^a^	xx (xx)	xx (xx)	xx (xx)	.xx
Temperature (°C)^a^	xx (xx)	xx (xx)	xx (xx)	.xx
Past medical history^b^	xx (xx%)	xx (xx%)	xx (xx%)	.xx
Diabetes^b^	xx (xx%)	xx (xx%)	xx (xx%)	.xx
High blood pressure^b^	xx (xx%)	xx (xx%)	xx (xx%)	.xx
Coronary artery disease^b^	xx (xx%)	xx (xx%)	xx (xx%)	.xx
Chronic obstructive pulmonary disease^b^	xx (xx%)	xx (xx%)	xx (xx%)	.xx
Stroke^b^	xx (xx%)	xx (xx%)	xx (xx%)	.xx
Cancer^b^	xx (xx%)	xx (xx%)	xx (xx%)	.xx
Heart failure^b^	xx (xx%)	xx (xx%)	xx (xx%)	.xx
···	···	···	···	···
Disease diagnosis^b^	xx (xx%)	xx (xx%)	xx (xx%)	.xx
Mild^b^	xx (xx%)	xx (xx%)	xx (xx%)	.xx
Moderate^b^	xx (xx%)	xx (xx%)	xx (xx%)	.xx
Initial symptoms^b^				
Fever^b^	xx (xx%)	xx (xx%)	xx (xx%)	.xx
Cough^b^	xx (xx%)	xx (xx%)	xx (xx%)	.xx
Fatigue^b^	xx (xx%)	xx (xx%)	xx (xx%)	.xx
Diarrhea^b^	xx (xx%)	xx (xx%)	xx (xx%)	.xx
Shortness of breath^b^	xx (xx%)	xx (xx%)	xx (xx%)	.xx
Sore throat^b^	xx (xx%)	xx (xx%)	xx (xx%)	.xx
Nausea^b^	xx (xx%)	xx (xx%)	xx (xx%)	.xx
Vomiting^b^	xx (xx%)	xx (xx%)	xx (xx%)	.xx
Taste and smell dysfunction^b^	xx (xx%)	xx (xx%)	xx (xx%)	.xx
Loss of appetite^b^	xx (xx%)	xx (xx%)	xx (xx%)	.xx
···	···	···	···	···
Concomitant medications	xx (xx%)	xx (xx%)	xx (xx%)	.xx
Antiviral drugs^b^	xx (xx%)	xx (xx%)	xx (xx%)	.xx
Anti-infective drugs^b^	xx (xx%)	xx (xx%)	xx (xx%)	.xx
Chinese patent medicine^b^	xx (xx%)	xx (xx%)	xx (xx%)	.xx
Others^b^	xx (xx%)	xx (xx%)	xx (xx%)	.xx

a Number, mean, standard deviation;

b Number, percentage.

### Imputation of missing data

Missing values of the primary and secondary outcomes will be carried forward from the latest observation data to the final results (LOCF method).

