### Withdrawal criteria and termination criteria

First, the investigator's decision to withdraw the patient is based on the following principles: 1) during the clinical trial, the patients develop diseases that are not suitable for further study; 2) patients with adverse events or serious adverse events are not suitable to continue the study, and 3) other conditions that the researchers believe will harm the health of the patients by continuing the study.

Second, patients can and should withdraw if they are unwilling to continue with the clinical trial. According to the provisions of the informed consent form, participants can withdraw at any time during the study. If patients have not explicitly proposed to withdraw but no longer accept medication and testing, as well as loss to follow-up, are regarded as 'withdrawal'. The reasons for withdrawal should be known and recorded as precisely as possible. Examples include consciously being unable to tolerate adverse events, inability to continue clinical research due to other reasons, or loss to follow-up without explaining the reasons. In electronic case report forms (eCRFs), the reasons for dropout will be recorded and the data analysis will include their last record.

Third, when reviewing the data prior to statistical analysis, it is up to the principal investigator (PI) and statisticians to judge whether an individual case is excluded. If one of the following events occurs, the two sides should consider whether the patient should be excluded based on the study's progress and the reasons for withdrawal and provide a detailed explanation: 1) After randomization, individuals not meeting the selection criteria or meeting the exclusion criteria of the research proposal are found; 2) The failure to take at least one dose of trial medication and the lack of any data post-randomization.

Fourth, the conditions for stopping early are as follows: 1) if a high incidence of serious adverse events is found during the research, the study should be suspended in time; 2) if during the research, significant mistakes are found in the research proposal or there are serious deviations in its implementation, making it difficult to evaluate the efficacy of drugs, the research should be stopped; 3) the ethics committee requests to suspend or terminate the research; 4) the administrative department cancels the research.

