### Sample size

The study hypothesis is SHHS group will be non-inferior to LHQW group. Clinicians and statisticians set the non-inferiority threshold at 10% and predicted that the recovery rate of clinical symptoms after 7 days of LHQW is about 87% and that of SHHS is 90% according to the literature reports on similar drugs. It is estimated that 94 patients for each group, ie. a total of 188 patients are needed to achieve the power of 80% at a one-sided statistically significant level of 0.025. Considering the possible dropout rate of 20%, 240 patients will be enrolled, that is 120 patients for each group.

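### Carrying the last observation forward as the rule for missing day-7 recovery can bias the full-analysis-set rate difference in either direction

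*Protocol article*

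**What the plan says.** The section on imputation of missing data consists of one rule, for primary and secondary outcomes alike: "Missing values of the primary and secondary outcomes will be carried forward from the latest observation data to the final results (LOCF method"). The withdrawal section agrees; for dropouts, "the data analysis will include their last record".

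Four other statements determine what the rule does:

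- **Endpoint.** The primary outcome is binary: recovery from fever, cough, sore throat and fatigue at the end of treatment on day 7. Inclusion criterion 3 requires at least one of these symptoms at entry. Table 1 schedules symptom records every day.
- **Analysis sets.** The FAS needs one dose and one visit. The PPS excludes patients whose primary outcome is missing. The primary analysis is run on both, and the article does not say whether both must show non-inferiority.
- **Dropout.** The sample size section states: "Considering the possible dropout rate of 20%, 240 patients will be enrolled, that is 120 patients for each group".
- **Blinding.** Treatment is open-label; assessors and statisticians are to be blinded.

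**The concern.** Every patient starts with symptoms, and the plan expects 87% to 90% to be free of them by day 7. A last record from day 2 or 3 will often show no recovery, whatever the patient's day-7 status would have been. This error is systematic, because it depends on how early the patient left.

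If both arms lose patients equally, carrying early records forward pulls the two rates together. If they lose patients unequally, the arm with more early losses is marked down. Patients and treating investigators know the treatment, so unequal loss is plausible. The decision rests on a 10-point margin, so a bias of several points in the FAS could change the conclusion.

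**Working it through.** **Inputs from the article:** LHQW 87%, SHHS 90%, margin 10 points, one-sided 0.025, power 80%, 94 per arm before dropout, 20% dropout, 120 per arm enrolled.

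**Assumptions, not in the article:** the missing share d in each arm; the share q of carried records that already show recovery; dropouts would have had the same day-7 rate as completers; a Wald 95% limit for the difference. The article names Clopper-Pearson, which is not in itself an interval for a difference.

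**Step 1: the plan's own figure.** n = (1.960 + 0.842)² × (0.87×0.13 + 0.90×0.10) / (0.03 + 0.10)² = 7.849 × 0.2031 / 0.0169 = 94.3 per arm. Power at 94 is 79.9%. Dropout: 94 / 0.8 = 117.5, so 118 per arm or 236 in total, against 240 stated. The sample size is not in dispute.

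**Step 2: the observed rate.** In each arm it is p(1 − d) + dq. False non-inferiority is the probability that the lower limit exceeds −10 points when the true rates are 77% (SHHS) and 87% (LHQW). Power uses 90% and 87%. Both are exact binomial with 120 per arm.

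| Missing SHHS / LHQW | q | Observed rates at 77% vs 87% | Difference (points) | False non-inferiority | Power |
|---|---|---|---|---|---|
| 0 / 0 | – | 0.770 vs 0.870 | −10.0 | 2.7% | 89% |
| 20% / 20% | 0 | 0.616 vs 0.696 | −8.0 | 5.1% | 56% |
| 20% / 20% | 0.5 | 0.716 vs 0.796 | −8.0 | 5.6% | 69% |
| 10% / 20% | 0 | 0.693 vs 0.696 | −0.3 | 37% | 97% |
| 10% / 20% | 0.5 | 0.743 vs 0.796 | −5.3 | 14% | 92% |
| 20% / 10% | 0 | 0.616 vs 0.783 | −16.7 | 0.1% | 10% |
| 20% / 10% | 0.5 | 0.716 vs 0.833 | −11.7 | 1.2% | 44% |

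The fifth row in full: SHHS 0.77×0.9 + 0.1×0.5 = 0.743; LHQW 0.87×0.8 + 0.2×0.5 = 0.796. The difference is −5.3, a shift of 4.7 points towards SHHS.

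**Step 3: reference without carried values.** With 96 completers per arm and loss unrelated to outcome, the difference stays at −10 points, false non-inferiority is about 2.8% and power about 82%.

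**Step 4: does equal dropout really double the error?** Only if the number of dropouts varies at random between arms. For q = 0 the computed standard error is √[(0.616×0.384 + 0.696×0.304)/120] = 6.11 points, so the observed difference must exceed −10 + 1.96×6.11 = +1.98. That is 9.98 points above the expected −8.

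- Random dropout counts: the true SD is also 6.11; 9.98/6.11 = 1.63, or about 5.1%.
- Exactly 24 dropouts per arm: the true SD is 0.8 × √[(0.77×0.23 + 0.87×0.13)/96] = 4.40; 9.98/4.40 = 2.27, or about 1.1% by exact calculation.

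**Step 5: carried recovery proportional to each arm's own rate.** With 20% missing in both arms and carried recovery at half of each arm's day-7 rate, the observed rates are 0.693 and 0.783 and the error is 3.8%. At the full day-7 rate the bias disappears.

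**The case against.** **The PPS is already a check.** It excludes missing primary outcomes, so nothing is carried forward there, and Table 3 prints it beside the FAS. In a simulation of 20% random dropout in both arms with q = 0, the error is 5.1% in the FAS, 2.7% in the PPS, and 1.4% if both must pass. This stands as mitigation. But the article sets no rule that both must pass, and a completer analysis does not protect against loss that depends on outcome.

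**A reader might infer that the rule generally inflates false non-inferiority.** The calculations do not support that. Excess dropout on SHHS lowers the error and costs power, and equal fixed dropout with q = 0 takes it to 1.1%. The 5.1% figure also cannot be charged to this rule alone: it is exactly what results from counting all missing patients as not recovered.

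**A reader might infer that the bias consumes a large part of the margin as a matter of course.** With equal dropout the shift is at most 2 points. Shifts near half the margin need unequal dropout, and the article gives no split. The 20% is a planning allowance, and patients who leave after recovering are carried forward correctly.

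**A reader might infer that standard errors are understated by a fixed amount.** They are not: in Step 4 the computed standard error equals or exceeds the true SD.

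**A reader might infer that patients who become severely ill will be counted as recovered.** The text does not exclude it, but it requires someone free of all four symptoms at the last record. Progression is not named as a withdrawal reason, and severe conversion is itself measured over 7 days.

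**The fuller plan may contain sensitivity analyses.** It may, so their absence from the article is no criticism. The rule itself is stated, twice.

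**Conclusion.** The point holds as one about the FAS result: carrying the last record forward is a stated rule, it is unsuited to a day-7 status in a fast-changing illness, and it can bias the rate difference in either direction. With equal 20% dropout the bias is 2 points at a true 10-point deficit. False non-inferiority is then about 5% to 6% if dropout counts vary at random, and 1.1% with exactly 24 dropouts per arm all carried as not recovered. Power is about 69% against 82% when half of the carried records show recovery. With a 10% vs 20% split and the same q, the shift is 4.7 points and the error about 14% when LHQW loses more; the error is about 1.2% and power about 44% when SHHS loses more.

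These sizes rest on the assumed split, on q, and on dropouts resembling completers. They show what the rule can do; they do not predict what it will do. The change should be made before the data are analysed, but the design and sample size are not affected.

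**What to change.** For the FAS primary analysis, replace the rule as follows:

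1. Count death or documented progression to severe disease by day 7 as not recovered.
2. Impute other missing day-7 status by multiple imputation within arm, using the daily symptom records and baseline disease class.
3. Add a tipping-point analysis over the imputed recovery rates in each arm, up to the worst case for the claim: all missing SHHS patients not recovered, all missing LHQW patients recovered.
4. Align the sentence on dropouts in the withdrawal section with the new rule.

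Counting every missing patient as not recovered should not be the substitute, because it reproduces the q = 0 rows of the table. Multiple imputation is not the only acceptable method, but it suits this trial because symptoms are recorded daily. The cost is plan wording and modest programming; the lower confidence limit may be slightly less favourable.

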**FIGURE 1 F1:**
[figure not shown]
Flow diagram of the study.

**TABLE 1 T1:** SPIRIT Schedule of enrollment, interventions and assessments.

Visit project	Study period									
	Screen period (baseline)	Allocation	Visit							
Time of visit (day)	-1	-1-0	1	2	3	4	5	6	7	8
1. Enrollment										
Eligibility screening	●									
Informed consent	●									
Demographic characteristics	●									
Diagnosis and medical history	●									
Comorbid conditions	●									
2. Interventions										
Random allocation		●								
Administration of study drugs			●	●	●	●	●	●	●	
3. Assessments										
Vital signs	●		●	●	●	●	●	●	●	●
Symptoms	●		●	●	●	●	●	●	●	●
Clinical assessment	●		●	●	●	●	●	●	●	●
Combined drugs	●		●	●	●	●	●	●	●	●
SARS-CoV-2 PCR testing	●		●	●	●	●	●	●	●	●
Adverse event monitoring**			●	●	●	●	●	●	●	●
4. Other work										
Distribute drugs			●	●	●	●	●	●	●	
Recover drugs										●
End of study summary										●

** Throughout the study, ongoing observations and recordings of when this occurred were made.

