### Secondary outcomes

The secondary outcomes are the recovery time of patients self-reported clinical symptoms, SARS-CoV-2 nucleic acid testing negative conversion time, and negative conversion rate, hospitalization time, antipyretic time, the incidence of severe patients, single symptom disappearance time, and disappearance rate.

Criteria for judging the curative effect:(1) Recovery time and cure rate of clinical symptoms: The recovery of clinical symptoms refers to the disappearance of the main symptoms, ie. fever, coughing, sore throat, and fatigue. The cure rate is defined as the proportion of patients whose clinical symptoms recovered after the end of treatment on the seventh day.(2) SARS-CoV-2 nucleic acid testing negative conversion time and negative conversion rate: Taking the first time of the two consecutive respiratory tract SARS-CoV-2 PCR negative tests (sampling interval at least 1 d) as the SARS-CoV-2 PCR testing negative time (the SARS-CoV-2 nucleic acid testing negative conversion time equals the SARS-CoV-2 PCR testing negative time–the diagnosis time of the patient).(3) Hospitalization time: the time from patient admission to discharge. The discharge standard refers to the release from isolation or discharge criterion of the protocol for diagnosing and treating novel coronavirus pneumonia (9th edition).(4) Antipyretic time: The body temperature is less than 37.4°C after treatment, for 24 h or more.(5) The conversion rate of turning to severe patients: the proportion of patients who develop severe infection 7 days after taking medicine.

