Taste and smell dysfunction^b^	xx (xx%)	xx (xx%)	xx(xx to xx)	.xx	xx (xx%)	xx (xx%)	xx(xx to xx)	.xx
Loss of appetite^b^	xx (xx%)	xx (xx%)	xx(xx to xx)	.xx	xx (xx%)	xx (xx%)	xx(xx to xx)	.xx
···	···	···	···	···	···	···	···	···
Time to negative conversion of SARS-CoV-2 PCR testing^a^	xx (xx)	xx (xx)	xx(xx to xx)	.xx	xx (xx)	xx (xx)	xx(xx to xx)	.xx
Rate of negative conversion of SARS-CoV-2 PCR testing^b^	xx (xx%)	xx (xx%)	xx(xx to xx)	.xx	xx (xx%)	xx (xx%)	xx(xx to xx)	.xx
Rate of conversion of severe patients^b^	xx (xx%)	xx (xx%)	xx(xx to xx)	.xx	xx (xx%)	xx (xx%)	xx(xx to xx)	.xx
Antipyretic time^a^	xx (xx)	xx (xx)	xx(xx to xx)	.xx	xx (xx)	xx (xx)	xx(xx to xx)	.xx
hospitalization time^a^	xx (xx)	xx (xx)	xx(xx to xx)	.xx	xx (xx)	xx (xx)	xx(xx to xx)	.xx

a Number, mean, standard deviation;

b Number, percentage.

Continuous data will be summarized using number, mean, standard deviation, minimum, maximum, median, upper and lower quartile. A t-test or Wilcoxon rank test will be applied to compare groups. ANCOVA will be considered to evaluate the influence of covariates. Chi-square test or Fisher exact test will be used to compare groups for categorical data. CMH-Chisquare test and logistic regression will be considered to explore the influence of covariates. Time-to-event data will be estimated by Kaplan-Meier method to compute the median and corresponding 95%CI. Log-rank test will be used for between-group comparison.

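### The unqualified LOCF rule can let one last negative PCR, or one last temperature below 37.4°C, stand in for required confirmation, and it conflicts with Kaplan-Meier censoring

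*Protocol article*

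**What the plan says.** All references are to the protocol article.

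- **Imputation of missing data (whole section):** "Missing values of the primary and secondary outcomes will be carried forward from the latest observation data to the final results (LOCF method". No outcome is exempted.
- **Secondary outcomes, criterion 2 (negative conversion):** "Taking the first time of the two consecutive respiratory tract SARS-CoV-2 PCR negative tests (sampling interval at least 1 d". Conversion is dated to the first test of the pair.
- **Secondary outcomes, criterion 4 (antipyretic time):** "The body temperature is less than 37.4°C after treatment, for 24 h or more".
- **Withdrawal criteria and termination criteria:** for dropouts, "the reasons for dropout will be recorded and the data analysis will include their last record".
- **Definition of analysis sets:** full analysis set (FAS) membership requires that randomised patients "use the medicine at least once, and have at least one visit will be analyzed using intention-to-treat analysis". Early dropouts therefore stay in.
- **Table 1:** "SARS-CoV-2 PCR testing" and vital signs are scheduled at screening and daily on days 1 to 8.
- **Analysis of secondary outcomes:** "Time-to-event data will be estimated by Kaplan-Meier method to compute the median and corresponding 95%CI", with a log-rank comparison. Table 4 also lays out the times as mean and SD, and the negative conversion rate as a count and percentage.
- **Sample size:** "Considering the possible dropout rate of 20%, 240 patients will be enrolled, that is 120 patients for each group".

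**The concern.** Both definitions are written so that one reading is not enough. LOCF supplies a second reading that nobody took. With a daily schedule, one copied value fills the next day's slot, which is all the two-test or 24 h condition needs. Because conversion is dated to the first test of the pair, the event time becomes the unconfirmed reading itself.

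At stake are the negative conversion rate and time, and the antipyretic time, in patients whose record ends on a first negative or first afebrile reading. For them the reported outcome would not be the defined one. For the two time outcomes the plan also gives conflicting instructions: under LOCF the patient has an event, and under Kaplan-Meier the patient is censored.

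**Working it through.** **1. The plan's own figures.** The only plan figure used here is dropout. The sample size around it reproduces:

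- n per arm = [0.87×0.13 + 0.90×0.10] × (1.960 + 0.842)² / (0.90 − 0.87 + 0.10)² = 0.2031 × 7.849 / 0.0169 ≈ 94.3. The plan has 94; rounding up gives 95.
- 188 / 0.80 = 235. The plan enrols 240.
- Planned dropouts per arm: 0.20 × 120 = 24.

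Nothing in this point changes the sample size.

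**2. One illustrative patient.** The last visit is day 4, PCR is positive on days 1 to 3 and negative on day 4.

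- Criterion 2 on observed data: one negative, so not converted.
- LOCF on daily PCR results: day 5 is copied as negative, giving two consecutive negatives and conversion dated day 4.
- LOCF on derived status: the last status is not converted, and it stays so.
- Kaplan-Meier without imputation: censored at day 3, the last day on which a first negative could have been confirmed by a second test.

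The same four lines apply to a single last temperature below 37.4°C.

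**3. Size by simple arithmetic.** Let q be the share of dropouts whose record ends on a single unconfirmed negative (not in the documents). Added points = 100 × 24q / 120 = 20q.

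| q (assumed) | extra conversions per arm | percentage points |
|---|---|---|
| 10% | 2.4 | 2 |
| 20% | 4.8 | 4 |
| 30% | 7.2 | 6 |

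**4. Size by simulation.** Assumptions not in the documents: last visit of dropouts uniform on days 1 to 7; exponential clearance with median 4, 6 or 8 days; a 0 to 20% chance per test of an isolated negative before clearance. Dropout is 20%. Entries are percent of an arm, rounded.

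| Median (days) | Stray negative | Observed pairs only | With LOCF | Complete follow-up to day 8 | Added by LOCF | Of these, not confirmed by day 8 |
|---|---|---|---|---|---|---|
| 4 | 0% | 63.6 | 65.6 | 70.3 | 2.0 | 0 |
| 4 | 20% | 70.4 | 73.8 | 77.3 | 3.4 | 0.7 |
| 6 | 0% | 49.8 | 51.4 | 55.4 | 1.6 | 0 |
| 6 | 20% | 59.6 | 62.9 | 65.8 | 3.4 | 1.0 |
| 8 | 0% | 40.7 | 42.0 | 45.4 | 1.3 | 0 |
| 8 | 20% | 52.3 | 55.7 | 58.1 | 3.3 | 1.2 |

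Adding normally distributed clearance (SD 2 days) and stray negatives up to 25% widens the added share to 0.9 to 4.1 points. Dividing by 0.20, that is 4.5% to 20.5% of dropouts. The part that would not have confirmed by day 8 is 0 to 1.5 points.

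**5. Between-arm effect of each way of computing the rate.** A stress case: no treatment effect, non-informative dropout, 10% dropout in one arm and 30% in the other (assumed; the plan has 20% overall). False difference in rate over 18 settings (exponential or normal clearance, median 4, 6 or 8 days, stray negatives 0 to 25%):

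| Rate | False difference (points) |
|---|---|
| Unconfirmed counted as not converted | 4.7 to 11.5 |
| LOCF on daily results | 2.5 to 8.8 |
| Kaplan-Meier cumulative proportion | about 0 |

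Counting unconfirmed patients as not converted gave the larger distortion in all 18 settings.

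**The case against.** **The rule may act on derived status.** The imputation sentence speaks of outcomes. A daily swab is not an outcome, and a copied value has no sample and so no sampling interval. If converted/not converted is what is carried forward, the problem vanishes. This stands as a possible reading, and the full analysis plan may settle it. But the article speaks of the latest observation data, and says that a dropout's last record enters the analysis. Both point to raw values. A reader might infer that the imputation rule cancels the confirmation rule outright; the text supports only that it can be read so.

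**Kaplan-Meier already protects the time outcomes.** It would, if LOCF did not also apply to them. The two sections need reconciling, and the binary conversion rate has no such protection.

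**The per-protocol set limits the exposure.** It excludes patients without the primary outcome, so most early dropouts are absent there. This stands: the effect lies mainly in the FAS.

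**Most of the added conversions are real.** This stands too. A reader might infer that all 1 to 4 points are false conversions, or that LOCF overstates the conversion rate. Neither follows. Most of the added patients would have confirmed by day 8, and in every simulated setting tabulated above the LOCF rate is below the complete-follow-up rate.

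**Simply counting unconfirmed patients as not converted would be worse.** As a main analysis this stands: it depends on dropout more than LOCF does.

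**Conclusion.** The point holds in a limited form. The plan states an LOCF rule without exemption that, read on the daily records, lets one last reading meet a two-test or 24 h definition. For the time outcomes it also contradicts the planned Kaplan-Meier and log-rank analysis.

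At 20% dropout and under the assumed clearance, stray-negative and dropout patterns, it adds about 1 to 4 points of unconfirmed PCR conversions per arm in the FAS. At most about 1.5 points are patients who would not have confirmed by day 8. The effect is zero if derived status is carried forward. Patients who had already met a definition before leaving are unaffected.

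The calculations concern PCR only. For temperature the event wrongly credited would be fever resolution, and no size is claimed.

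A reader might infer a bias between arms from the open-label design. The documents give no sign that dropout will differ, and the 10% versus 30% case is a stress scenario. A reader might also extend the point to the non-inferiority conclusion. This point does not touch the primary test, since the confirmation rules belong to secondary outcomes. The change is worth making because it is a stated rule and costs almost nothing.

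**What to change.** In the missing-data section, and matching it in the analysis of secondary outcomes:

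1. Exempt negative conversion (time and rate) and antipyretic time from LOCF.
2. Derive both from observed confirmations only: two actual negative samples at least one day apart, and actual readings covering 24 h or more.
3. In the Kaplan-Meier and log-rank analysis, censor unconfirmed patients at their last confirmable assessment.
4. Estimate the negative conversion rate as the Kaplan-Meier cumulative proportion at the end of follow-up.
5. Show the rate with unconfirmed patients counted as not converted, and the LOCF rate, only as sensitivity analyses, because both differ between arms when dropout differs.

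Cost: a few sentences, with no change to sample size, visits or data collection. The downside is that the Kaplan-Meier rate assumes non-informative dropout; the two sensitivity rates show how far the result depends on how dropouts are handled.
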